### Recruitment

Recruitment will take place through notices at the University of Hamburg as well via advertisements in local newspapers. By the use of a snowball concept, we will ask all participants to advertise the study and provide additional participants. In previous experiments, we have found that this strategy was particularly useful to find more participants.

### Data collection

The data collection will take place in the premises of the University of Hamburg, Department of Human Movement Science. Before the study is carried out, the participants are instructed not to do any strenuous sport, as this can already mean pre-fatigue and thus falsify the data. The participants are also informed in advance of the study that physical and mental fatigue may occur during and after the study. In addition, care is taken to ensure that the study is carried out at similar times of day so that a drop in performance over the course of the day can be taken into account.

#### Data protection

The data collected within the context of the study following the declaration of consent of the participants are covered by confidentiality and the provisions of data protection law. The study prioritizes data confidentiality and security through initial pseudonymization by generating a code followed by anonymization, in accordance with the University of Hamburg’s data protection guidelines. Participants in the study can be identified by pseudonyms linked to their personal details, allowing them to request access to their personal scores via the secure coding list. Only the research team will have access to this list, and participants can request the removal of their personal data until it is deleted. Personal data together with the coding list and research data will be stored separately, with access restricted to the principal investigator and authorized staff, and no third-party transfers will be permitted. The coding list will be maintained until data evaluation is completed.

#### Harms

Wearing an exoskeleton can cause a feeling of discomfort (53), however it is not expected that an exoskeleton will harm a participant.

In the event that the participant shows or expresses strong symptoms of exhaustion or discomfort, the study is terminated without any disadvantage to the participant. If necessary, the study is repeated on another day.

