#### Physical fatigue session

A fatigue session takes place, following a randomized order, e.g., before the PILE task or before the nailing task. The fatigue session will be performed in 3 sets, with a 2-min calf raise and a 2-min front raise with weight per set, with the front raise in the second set only being performed for the second minute. The weight of the men is 5 kg and that of the women 2.5 kg. There will be a break of 60 s between the sets. During the exercise, a metronome runs at 60 bpm, and the front and calf raises are to be performed to this beat. Before the start of the fatigue session, the maximum body height will be determined individually on the anthropometer by the test person standing upright and bringing their feet into plantar flexion. This determined height should be reached during each exercise. The level of fatigue will be determined using EMG power spectral shifts (Fast Fourier Transform) in combination with a visual analog scale of peripheral fatigue.

Questionnaires on acceptance and discomfort of the conditions with exoskeleton use will be filled out after the experimental procedure.

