#### Speed accuracy trade offs (Fitts task)

The Fitts task is a standard motor control experiment in which participants move quickly between two targets of different sizes and distances (44). The aim is to assess the speed and accuracy of the target movements. The difficulty of the task is determined by a difficulty index, which is calculated based on the size and distance of the targets. The researchers manipulate the task conditions to investigate factors that influence movement time and accuracy. Key measures include movement time and error rate, which provide insight into the trade-off between speed and accuracy in motor control. The Fitts task is often used in human-computer interaction and to assess motor skills.

The Borg rating of perceived exertion is used together with the SUS and the NASA-TLX questionnaires to answer research question 1d, investigating the effects of using an upper body exoskeleton on comfort/discomfort, acceptance and ease of use during task performance.

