### Participant timeline

The study will be conducted over two separate days to mitigate potential carryover effects and ensure the avoidance of additional fatigue symptoms. On each day, participants will undergo the assigned conditions for both tasks in a randomized order, minimizing the impact of confounding variables. The sequence of conditions will be counterbalanced across participants to control for order effects.

First, the participants are welcomed and informed in writing and verbally about the aim and conduct of the study. This is followed by the recording of the anthropometric data and personal data. Then the preparations for the surface electromyography begin, including the application of the electrodes and the pre-tests (MVC). The suit for the Xsens sensors is then applied and a calibration is carried out. Finally, the sensor and the calibration for the fNIRS are carried out.

The first session then begins, depending on which task was selected first for the person. The person is then either fitted with the exoskeleton and begins the first task (Physical Performance Task or Precision Task) or performs this without the exoskeleton. If the fatigue protocol is already planned for the person at the beginning based on the randomization, this is carried out without the exoskeleton before the start of the task.

After completion of the first task, an individual break is taken before the second task begins. After completing both tasks, the person is asked to complete the questionnaires.

Due to the activity of overhead work, which already involves increased exertion because of the non-ergonomic posture, and the additional activity of screwing, physical fatigue may increase. Therefore, physical exertion is subjectively documented via the Borg scale (49) after each test session. Additionally, test sessions are spread over 2 days.

Individual breaks will be provided between each test session due to possible mental and physical exertion during the tests (Figure 3).

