### Sample size

The sample size was calculated on the outcome of muscle activity using G*power (*a priori*, ANOVA with repeated measures and interaction effect) with 2 groups (male/female), 2 tasks (Physical Performance Task, Precision Task), 2 conditions (with/without exoskeleton), and 2 fatigue protocols (with/without fatigue protocol) estimating an effect size of 0.25, an alpha error rate of 0.05 and a statistical power of 0.80, resulting in *N* = 36 participants for each group. With an estimated drop of 20% we will include a total of *N* = 80 (40 female/40 male) healthy participants with male and female participants equally.

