### Gender differences

With respect to the research questions, we hypothesize that potential gender differences will be observed within the muscle synergies. We think that the exoskeleton use will reduce shoulder muscle activity significantly [e.g., (54)] but first studies suggest that women might have less muscle activation in the shoulder muscles while wearing an exoskeleton (33). On the other hand, with respect to the design and the weight of the exoskeleton, women potentially could use different movement patterns to manage the tasks (56) due to differences in biomechanical and anthropometric trunk muscle geometry of females and males (56, 57). We anticipate that women show more bending backwards movements including a higher compensatory muscle activation in the abdominal and neck muscles. However, this idea has to be proven within our experimental design.

Moreover, as women are merely not integrated into the iterative designing processes of exoskeletons, yet, we propose more discomfort and less usability in the ratings by the women. This discomfort especially will be reported for the shoulder region (41).

In line with the cognitive resource theories (36), this discomfort might lead to more attentional resources spending on the discomfort and less resources available for the working DT situation. This will increase the cognitive-motor interference especially in the DT situation and could be observed with more cortical activation in the prefrontal cortex [*cf.* (35)]. Moreover, the working accuracy will decrease (58).

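### Strong discomfort can end a participant's run before the day's questionnaires are reached, and a repeat is allowed without saying which rating counts, so discomfort ratings may be lost or replaced because of their value and the gender difference may be understated

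*Protocol article*

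**What the plan says.** Three parts of the protocol article bear on this.

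- **Stopping and repeating (Harms).** "In the event that the participant shows or expresses strong symptoms of exhaustion or discomfort, the study is terminated without any disadvantage to the participant". The next sentence reads: "If necessary, the study is repeated on another day". Neither sentence says whether ratings are taken at the stop, or which attempt is analysed after a repeat.
- **When ratings are collected.** Participant timeline: "After completing both tasks, the person is asked to complete the questionnaires". Physical fatigue session: "Questionnaires on acceptance and discomfort of the conditions with exoskeleton use will be filled out after the experimental procedure". Borg exertion is collected more often: "Therefore, physical exertion is subjectively documented via the Borg scale (49) after each test session".
- **What the ratings are for.** "The Borg rating of perceived exertion is used together with the SUS and the NASA-TLX questionnaires to answer research question 1d", which covers comfort or discomfort, acceptance and ease of use. The Gender differences section gives the expected direction: "we propose more discomfort and less usability in the ratings by the women".

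**The concern.** One of the two triggers for ending a run is strong discomfort, and discomfort is what research question 1d measures. The questionnaires come later, once both tasks are done. Someone stopped during either task has not reached them for that day. If the session is then repeated, the available rating may come from a second exposure to the device.

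Whether a rating exists, and which attempt it describes, can therefore depend on how bad the rating would have been. The protocol expects worse ratings in women, so a common tolerance threshold would remove more of the women's high ratings than the men's and pull the comparison towards no difference. Discomfort as a barrier to adoption, particularly by women, is one of the study's stated interests. An analysis plan can model missing ratings, but it cannot recover ratings that were never collected.

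**Working it through.** **The plan's own figures.** There is none to reproduce on this point. The document gives no SD for discomfort, no expected gender difference in it and no stop rate. The sample size calculation concerns muscle activity. All sizes below are illustrations under assumptions.

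**Order of events.** Task 1, break, task 2, questionnaires. A stop under the Harms section during task 1 or 2 comes before the questionnaires. Borg ratings from sessions already finished, and questionnaires from a completed first day if they are given daily, would exist. An abort of the PILE task under that task's own termination criteria is a task end point and is not counted here.

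**Model.** Discomfort is N(0, 1) in men and N(d, 1) in women, and every rating above a common threshold c is lost. The mean of the remaining ratings in a group with mean μ is μ − φ(c − μ)/Φ(c − μ), and the share stopped is 1 − Φ(c − μ).

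**Worked case: d = 0.5, c = 1.645**

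- Men: 5.0% stopped; mean of the rest 0 − 0.1031/0.9500 = −0.109.
- Women: c − d = 1.145, so 12.6% stopped; mean of the rest 0.5 − 0.2072/0.8739 = 0.263.
- Observed difference 0.263 + 0.109 = 0.372. Loss (0.5 − 0.372)/0.5 = 26%.
- Of 40 per gender, about 2 men and 5 women are stopped.

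**Range**

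| True d (SD) | c | Men stopped | Women stopped | Observed (SD) | Loss |
|---|---|---|---|---|---|
| 0.3 | 2.5 | 0.6% | 1.4% | 0.28 | 6% |
| 0.5 | 2.5 | 0.6% | 2.3% | 0.46 | 8% |
| 0.5 | 2.0 | 2.3% | 6.7% | 0.42 | 17% |
| 0.5 | 1.5 | 6.7% | 15.9% | 0.35 | 30% |
| 0.8 | 1.5 | 6.7% | 24.2% | 0.53 | 34% |
| 0.8 | 1.282 | 10.0% | 31.5% | 0.48 | 40% |

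The last row means 0.315 × 40 ≈ 13 of 40 women stopped. At d = 0.5 with 40 per group, the power of a two-group comparison falls from 0.61 to between 0.57 (c = 2.5) and 0.42 (c = 1.5).

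**Weaker link between stopping and rating.** If the tendency to stop correlates only 0.7 with the rating, the remaining mean becomes μ − 0.7 × φ/Φ, evaluated at the stopping threshold. For d from 0.3 to 0.8 and 2% to 10% of men stopped, the loss is 9% to 28% if the tendency to stop carries the full gender difference. It is 6% to 18% if it carries 0.7 of that difference.

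**Does the direction always hold?** No. With a true difference of 0.5 SD, removing a fixed top share q of a group lowers its mean by φ(z)/(1 − q), where z is the 1 − q normal quantile. This is 0.109 for q = 5% and 0.195 for q = 10%.

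- Top 5% of both genders lost: 0.50, no bias.
- Top 10% of women only: 0.5 − 0.195 = 0.31.
- Top 10% of men and 5% of women: 0.5 − 0.109 + 0.195 = 0.59.
- Top 10% of men only: 0.5 + 0.195 = 0.70.

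Stops unrelated to discomfort leave the difference unbiased.

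**What the model omits.** It treats every stopped rating as permanently lost. A repeat that yields a rating would change the loss by an amount that depends on how the second rating differs from the first. The documents give nothing on that.

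**The case against.** The strongest reply is that the timing sentences describe the ordinary course of a participant who finishes, and do not forbid taking ratings at an early stop. The wording in the Physical fatigue session section could even cover a procedure that ended early. Borg, which also serves question 1d, is taken after each session by body region, and testing spans two days, so a stopped participant may already have ratings. The stop rule also covers exhaustion, half of the conditions have no exoskeleton, and the fatigue protocol is done without it, so many stops may have nothing to do with the device. The article is a condensed account, and handling of missing ratings may be set out elsewhere.

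Most of this stands, and it limits the point. A reader might infer that stopped participants give no rating at all, that a repeat overwrites the first attempt, that terminations will go unreported, or that the gender difference is certainly understated. The documents support none of these: the first goes further than the text, the second and third are not written, and the fourth depends on who is stopped and why.

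The reply does not remove the gap. The stop, the repeat and the collection time are conduct rules that the article itself fixes. Followed as written, they leave SUS, NASA-TLX, acceptance and discomfort ratings for the stopped day uncollected, or collected only at a repeat.

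**Conclusion.** The concern holds in conditional form, with moderate confidence. The stop rule and the collection time together allow ratings for question 1d to be lost or replaced in a way that depends on their value. The gender difference may be understated if three things hold: women have more discomfort, as hypothesised; stops are driven by discomfort; and the threshold is similar for both genders.

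The size cannot be derived from the documents. With all stopped ratings lost, the illustrations run from 6% to about 40% of the true difference. The upper end needs nearly a third of the women to be stopped, which is implausible in healthy adults aged 18 to 45. With stop rates of a few percent and a true difference of 0.5 SD, the loss is nearer 8% to 17%. It is nil if stops are unrelated to discomfort. The point is worth correcting because it is cheap to prevent and cannot be repaired after data collection.

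**What to change.** Reconcile the Harms section with the Participant timeline and the Physical fatigue session section:

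1. When a run is terminated, collect the Borg, NASA-TLX, SUS, discomfort and acceptance ratings before the participant leaves, and flag them as coming from an incomplete run.
2. For these subjective ratings only, keep the rating at termination as the primary record and use the repeat rating in a sensitivity analysis. sEMG, fNIRS and motion data may come from the repeated run. Extending the rule to them would put truncated recordings into the main analysis, including muscle activity, on which the sample size was based.
3. Record each termination with its reason, and report counts by gender, exoskeleton condition and fatigue condition.

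The stop rule itself is unchanged. The cost is a few lines of wording, one field in the case record and a few minutes of questionnaires for those stopped. The downside is that a few ratings refer to incomplete runs and must be interpreted as such.

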#### Informedness

The participants are fully informed about the background and the objectives of the research project (respective subject information).

Additionally, to enhance participant retention, we will keep them engaged and informed by sharing the study results.

#### Consent

Participation in the studies is voluntary. The participants are verbally and in writing informed and have sufficient time to understand the content of the study. They can withdraw from the study at any time without giving reasons and without incurring any disadvantages.

In the event of withdrawal of consent during the project period, the data already collected will be deleted upon request. In this case, the pseudonymization will be canceled by the respondent himself/herself, and the disclosure of the code, as otherwise the data set cannot be determined.

The subjects will sign the attached consent forms before the start of the study. These contain detailed participant information, information about OEMG studies as well as information about video recordings and fNIRS studies.

### Data monitoring

The whole author group will be involved into the data monitoring hosting meetings once a month. Following the data collection, the raw data will be reviewed, and possible elimination of poor data will be made (cleaning of the data set). Standardized procedures will be applied to the sEMG data sets, the fNIRS data set, and the questionnaires.

The raw data of the 3D motion analysis will be extracted, processed, and evaluated via MATLAB (Matlab R2019b, Massachusetts, USA).

The video recordings are reviewed to ensure that all measuring instruments are synchronized.

### Statistical analysis

All data will be processed via SPSS 29.0 and evaluated using suitable statistical procedures at the significance level *α* = 0.05. These statistical procedures depend on concrete questions and include variance analyses as well as descriptive procedures.

For the analysis of the movement data (Xsens), repeated measures ANOVA will be carried out with regard to upper body flexion, lateral flexion and rotation with a comparison between the different scenarios. Furthermore, we will conduct Bonferroni *post-hoc* tests for between-subject analysis regarding differences between (1) using an exoskeleton, and (2) fatigue protocol. In addition, an SPM analysis will provide information on the sections of the activity in which a change over time can be detected.

For the analysis of muscular activation, an ANOVA with repeated measures is also used for the comparisons between the scenarios, as well as Bonferroni *post-hoc* tests for between-subject comparison. In addition, a Statistical Parameter Mapping (SPM) analysis can also be carried out here, which illustrates the deviations over time.

The subject-specific muscle synergies will be classified through k-means clustering using the Hartigan-Wong algorithm independently for each group and condition. For statistical analysis of muscle weights between groups two-way analysis of variance (ANOVAs) will be carried out, which in case of statistical significance will be followed by post-hoc comparisons through pairwise t-tests with Benjamini-Hochberg adjusted *p*-values. For all muscle weightings that show significant differences, effect sizes (Cohen’s d) will be calculated. Furthermore, the activation patterns will be analyzed through the calculation of center of activity, as well as the full width at half maximum (FWHM). Additional discretes for analysis can be number of synergies per subject and percentage of unclassifiable synergies.

All objective data recordings will be synchronized via LSL and processed with specific MATLAB pipelines.

For the analysis of the cognitive data (fNIRS), as well as the subjective perceived exertion via the Borg scale, an ANOVA with repeated measures is carried out in each case.

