Are there gender effects of using an upper body exoskeleton for both tasks regarding:Muscle synergies?Upper body posture?Cognitive resources?Comfort/discomfort, acceptance and usability?Are there gender effects of using an upper body exoskeleton for both tasks under previous physical fatigue for:Muscle synergy?Upper body posture?Cognitive resources?

The research questions will be answered using a randomized crossover study design (*cf.*
Figures 1, 2). Participants of each gender will be randomly assigned to different sequences of interventions, ensuring a balanced distribution of order effects. This design allows each participant to serve as their control, contributing to internal validity.

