## Methods and analysis

### Trial design

This study includes a randomized experimental cross-sectional design comparing males and females (parallel groups). This means that each participant runs through each scenario in a randomized order.

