### Experimental set-up/intervention

The experimental design includes two physical tasks (1. Physical Performance Task and 2. Precision Task) in four randomized conditions (with and without exoskeleton and with and without prior physical fatigue; *cf.*
Figures 1, 2):

Physical Performance Task (PILE task) at shoulder height:Participants will perform the Physical Performance Task at shoulder height, both with and without the exoskeleton. This task aimed to assess the impact of the exoskeleton on physical performance under normal working conditions.

Precision Task (nailing following the Fitts paradigm) at overhead height:The Precision Task involves overhead nailing activities following the Fitts paradigm (43, 44) (three predefined templates into which the nails must be precisely inserted.), simulating tasks requiring precision and skill. Participants will execute this task with and without the exoskeleton, allowing the evaluation of the exoskeleton’s influence on tasks demanding fine motor skills.

Randomization will be done by the online program www.randomizer.org.

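### The posture post-hoc tests treat exoskeleton and fatigue as between-subject factors although both are crossed within participants, and the Statistical analysis section names no gender × exoskeleton test for posture, EMG, fNIRS or Borg

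*Protocol article*

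**What the plan says.** **The questions.** The list that closes the Introduction of the protocol article has two research questions. The first begins "Are there gender effects of using an upper body exoskeleton for both tasks regarding", the second "Are there gender effects of using an upper body exoskeleton for both tasks under previous physical fatigue for". Both ask whether the exoskeleton acts differently in women and men.

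**The design.** Trial design sets males against females as parallel groups and adds that "each participant runs through each scenario in a randomized order". Experimental set-up/intervention lists "four randomized conditions (with and without exoskeleton and with and without prior physical fatigue"). The text after the research questions says of the crossover: "This design allows each participant to serve as their control, contributing to internal validity".

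**The analysis.** The Statistical analysis section says the following.
- Posture: a repeated measures ANOVA on "upper body flexion, lateral flexion and rotation with a comparison between the different scenarios", then Bonferroni post-hoc "tests for between-subject analysis regarding differences between (1) using an exoskeleton, and (2) fatigue protocol".
- Muscular activation (EMG): a repeated measures ANOVA comparing scenarios, with Bonferroni post-hoc tests called between-subject but with no factor named.
- fNIRS and Borg: a repeated measures ANOVA for each, with nothing further.
- Muscle synergies: a two-way ANOVA of muscle weights between groups.

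**The sample size.** The Sample size section uses muscle activity, a repeated measures ANOVA with an interaction effect, two gender groups, effect size 0.25, alpha 0.05 and power 0.80. It arrives at 36 per group.

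**The concern.** There are two linked problems.

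First, the posture post-hoc sentence assigns two factors to the wrong stratum of the design. A with/without-exoskeleton difference is measured inside each person, and so is a with/without-fatigue difference. An analyst who follows the sentence would compare the two sets of runs as if different people had produced them, and would lose the precision that the crossover was chosen to give.

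Second, for four outcomes the section does not name the term that answers the research questions. A comparison of scenarios estimates the effect of the device averaged over women and men. It can be large and highly significant when the device acts identically in both. If the gender test is left unnamed, it may be chosen after the results are seen, or the report may hold exoskeleton and fatigue effects without a stated test of the question.

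**Working it through.** **1. Which factors lie within and which between**

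| Factor | Design sections | Posture post-hoc sentence |
|---|---|---|
| Exoskeleton with/without | within (every participant has both) | between-subject |
| Fatigue with/without | within (every participant has both) | between-subject |
| Gender | between (parallel groups) | not mentioned |

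The sentence contradicts the design for both factors that it lists and omits the only factor to which its label applies.

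**2. The protocol's own sample-size figure**

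The within-person correlation ρ is not given, so it is assumed here. I take 0.25 as Cohen's f, sphericity, and the standard noncentral-F formula for a within-between interaction:

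λ = f²·N·m/(1−ρ), df1 = (k−1)(m−1), df2 = (N−k)(m−1).

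With k = 2 gender groups and m = 2 measurements, 80% power needs a total of 66, 46 or 34 people at ρ = 0, 0.3 or 0.5. With m = 4 the totals are 46, 32 and 24, and with m = 8 they are 30, 22 and 16. None of these is 72 (36 per group), so the figure is not reproduced from the stated inputs. That is a separate matter. It is used here only to see whether the stated N carries the interaction.

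**3. Cost of running the posture post-hoc tests as worded**

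Inputs: n = 72 people (36 per group) and equal variances; ρ is assumed.

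- Paired standard error: σ√(2(1−ρ)/n). Independent-sample standard error: σ√(2/n). Ratio: 1/√(1−ρ).
- A paired test with 71 degrees of freedom has 80% power at a noncentrality of 2.84.
- The independent-sample test rejects at |t| > 1.977 (142 degrees of freedom). Its statistic has standard deviation of about √(1−ρ), so on the paired scale the threshold is 1.977/√(1−ρ).
- Power ≈ 1 − Φ(1.977/√(1−ρ) − 2.84). True type I error ≈ 2[1 − Φ(1.977/√(1−ρ))].

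| ρ (assumed) | SE ratio | Threshold | Power (paired: 0.80) | Type I error (nominal 0.05) |
|---|---|---|---|---|
| 0.3 | 1.20 | 2.36 | 0.68 | 0.018 |
| 0.5 | 1.41 | 2.80 | 0.52 | 0.005 |
| 0.7 | 1.83 | 3.61 | 0.22 | 0.0003 |

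Simulation with 80,000 data sets per row gives power of 0.68, 0.52 and 0.23, in agreement.

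The loss depends on the size of the effect. At a standardised difference of 0.5, simulated power falls only from 0.94, 0.987 and 1.00 (paired) to 0.89, 0.92 and 0.97.

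**4. A scenario comparison against the research question**

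In 20,000 simulated data sets of 36 women and 36 men, the exoskeleton effect was the same in both genders (standardised difference 0.5, ρ = 0.5). The paired scenario comparison was significant in 98.7% of them. The gender × exoskeleton test was significant in 5%, its nominal false-positive rate. The first result says nothing about the second.

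**5. Does naming the interaction require more people?**

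Take gender × exoskeleton with k = 2, m = 2 and f = 0.25. For 72 completers at ρ = 0, λ = 0.0625·72·2/1 = 9.0.

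| Completers | ρ = 0 | ρ = 0.3 | ρ = 0.5 |
|---|---|---|---|
| 72 | 0.84 | 0.94 | 0.987 |
| 64 (80 less 20%) | 0.795 | 0.91 | 0.976 |

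At the stated effect size the planned number is enough, apart from a negligible shortfall at 64 completers with no correlation. These figures are for the two-way term of the first research question.

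**The case against.** A reader might infer that all four analyses (posture, EMG, fNIRS, Borg) test exoskeleton and fatigue as between-subject factors with the wrong error term, and therefore cannot test the research questions. The document does not support that.

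- The explicit mislabelling is in the posture post-hoc tests only. The EMG sentence names no factor and, as gender is the only between-subject factor, may well mean gender. For fNIRS and Borg there is neither a scenario comparison nor a between-subject test.
- The main test for all four outcomes is a repeated measures ANOVA, which uses the within-subject error term for exoskeleton and fatigue. The wrong term enters only at the post-hoc step, and only if the sentence is followed literally. Some would read that sentence as gender comparisons within the exoskeleton and fatigue conditions.
- The Abstract describes a mixed-measure design grouped by gender, and the Sample size section gives gender groups and an interaction for muscle activity. A mixed model with an interaction was evidently intended.
- An article may leave the full list of model terms to a document not shown.

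Most of this stands and limits the scope. Two things remain. Placing exoskeleton and fatigue under a between-subject heading is a statement that contradicts the design, not a detail left out. And the Sample size section covers muscle activity only and does not say which interaction is meant; the Statistical analysis section instead describes the posture and EMG comparisons as between scenarios.

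**Conclusion.** The point holds in two parts. For posture, the post-hoc tests of exoskeleton and fatigue are assigned to a between-subject analysis, against the crossover design. For posture, EMG, fNIRS and Borg, the Statistical analysis section names no gender × exoskeleton term, although that term is the research question and the study is sized on an interaction with gender groups.

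If the posture sentence is followed literally, standard errors are 20% to 83% too large for ρ from 0.3 to 0.7, and a contrast with 80% paired power drops to between 68% and 22%. These figures rest on assumed correlations, equal variances and 72 completers. For larger effects the loss is modest. The direction is conservative throughout, and the loss concerns exoskeleton and fatigue contrasts rather than the gender interaction itself.

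The second part is a failure to name the test. It does not show that the test will not be done. It should still be settled before the data are analysed.

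**What to change.** In the Statistical analysis section:

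1. State, for posture, EMG, fNIRS and Borg, a mixed ANOVA or linear mixed model with gender between subjects and exoskeleton and fatigue within subjects, for each task.
2. Name gender × exoskeleton as the test for the first research question. For the second, name gender × exoskeleton × fatigue, or gender × exoskeleton within the fatigued runs, and say which.
3. In the posture post-hoc sentence, replace the between-subject label by within-subject (paired) contrasts for exoskeleton and fatigue. Reserve between-subject comparison for gender, and name the factor in the EMG sentence.
4. In the Sample size section, say which interaction the calculation refers to, so that it matches the named test.

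The cost is wording only. It needs no new data or measurements and, at the stated effect size, no larger sample.
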